**Introduction**

Delivering Continuous Positive Airway Pressure (CPAP) has become the standard of respiratory care in neonates. Nasal CPAP remains an efficacious way of delivering CPAP in preterm neonates with respiratory distress^(1)^. With the increasing use of nasal CPAP, the safety and comfort associated with nasal CPAP has come into the forefront. The reported incidence of nasal injuries associated with use of CPAP is 20% to 60% ^(2-6)^ and range from simple blanching of the nasal tip to serious nasal septal necrosis and septal drop. These nasal injuries may lead to long-term consequences including cosmetic problems. Local pressure at the nasal interface compounded by the cutaneous vulnerability and certain anatomical peculiarities such as end-vascularization of the Columella and nostrils are the principle factors reported to be responsible for the nasal injuries^(7)^. Lower gestational age, lower birth weight and longer duration of CPAP and neonatal intensive care unit stay have been reported as risk factors for nasal injury^(3,6)^. Apart from these factors, type of nasal interface and CPAP delivery devices may be important determinants of nasal injury associated with nasal CPAP. In this study we plan to evaluate if rotation of nasal interface reduces the incidence of nasal injury in comparison to use of a single interface (prong or mask).

**REVIEW OF LITERATURE**

*Burden of Disease*:

Respiratory disorders are the commonest cause of neonatal morbidity requiring intensive care. The incidence of respiratory distress in preterm neonates varies from 4 to 7 per 100 live births. Respiratory Distress Syndrome (RDS) constitutes one third of cases of respiratory distress in preterm neonates.^(8)^ The risk of RDS is inversely proportional to the gestational age, with an incidence of about 50% in babies less than 30 weeks of gestational age.^(9)^ RDS is the commonest disorder requiring assisted ventilation in both developed and developing countries. Assisted ventilation and surfactant has been the standard of care for last two decades.^(10)^ Respiratory support practice in newborn intensive care continues to evolve rapidly. A host of new modalities and techniques have become available for the infant with respiratory insufficiency over the past decade.

*Historical Aspect and known facts*:

The first use of CPAP in neonates was reported by Gregory et al in 1971. It was given by a head chamber (Gregory box) and was instrumental in decreasing the mortality in RDS from 35 -55% to 15 -20%.^(11)^The primary role of the CPAP is to support the smaller airways and to prevent generalized atelectasis of surfactant deficient alveoli. This leads to improvement in the oxygenation and ventilation by opening of poorly ventilated air spaces, relieving local vasoconstriction and decreasing intrapulmonary right to left shunt. In the late 1970s and 1980s, infant ventilators were developed rapidly. The focus for respiratory care of the newborns shifted gradually towards mechanical ventilation, and the use of CPAP declined. Though invasive mechanical ventilation decreased the mortality, there was no considerable change in the incidence of bronchopulmonary dysplasia (BPD).

A study conducted by Avery et al in 1987 comparing the outcome in eight different academic centers in USA noted that the best survival without BPD was noted in institutions that used nasal CPAP extensively for the stabilization of very low birth weight (VLBW) babies.^(12)^ Schmölzer performed a meta-analysis and included 4 trials (COIN, SUPPORT, CURPAP and VON) with a total of 2780 preterm infants (<32 weeks GA). The pooled results for the combined outcome death or BPD showed a reduction in favour of delivery room NCPAP compared to intubation with a relative risk 0.90 (0.83-0.98 95% CI) and numbers needed to treat (NNT) of 25^(13)^. Currently nasal continuous positive airway pressure (NCPAP) is the most commonly used respiratory support for newborn infants. It is a technique for non-invasive respiratory support of both term and preterm infants with respiratory distress.

## Nasal Interface

The success of nCPAP is to a large extent dependent on the appropriate selection of a nasal interface. short binasal prongs, long nasopharyngeal prongs or nasal masks are the interfaces currently available to deliver the NCPAP. Meta-analysis by De Paoli AG et al ^(14)^ concluded that short binasal prongs are more effective than nasopharyngeal prongs. There are only few randomised controlled trials which have compared the nasal prong and nasal mask as interfaces for nasal CPAP in VLBW neonates with respiratory distress syndrome .

S-C Yong et al(2005)^(15)^Compared the incidence of nasal trauma associated with the use of prong or mask during nasal continuous positive airway pressure (nCPAP) support in very low birthweight (<1501 g) infants. They conducted a randomised controlled clinical trial at a tertiary care university hospital, Department of Paediatrics, Kuala Lumpur, Malaysia. All very low birthweight infants admitted to the neonatal intensive care unit between July 2001 and December 2003 who received nCPAP through the Infant Flow Driver were randomised to the use of either nasal prong or mask. The nasal cavity of these infants was inspected daily during the first week and then weekly until they were weaned off nCPAP. Of the 89 infants recruited, 41 were randomised to the mask group and 48 to the prong group. There was no significant difference in the incidence of nasal trauma between the two groups (p = 0.5). The primary site of trauma was at the junction between the nasal septum and the philtrum in infants in the mask group and the walls of the nasal septum in the prong group. Logistic regression analysis showed that duration of nCPAP was the only significant risk factor associated with development of nasal injury, after birth weight, gestational age, and nasal device used had been controlled for (adjusted odds ratio 1.04; 95% confidence interval 1.01 to 1.07; p = 0.003.

Emily A. Kieran et al 2012^(16)^ compared nasal mask vs nasal prong as an interface to deliver nCPAP with need for ventilation as primary outcome and nasal injury as secondary outcome.120 infants were enrolled. Thirty-two of 62 (52%) infants randomly assigned to prongs were intubated within 72 hours, compared with 16/58 (28%) of those randomly assigned to mask (P = .007). Nasal injury occurred in 2 infants in each group with no statistically significant difference. Authors concluded that in premature infants, NCPAP was more effective at preventing intubation and ventilation within 72 hours of starting therapy when given via nasal masks compared with nasal prongs with no increased risk of nasal injury.

Katherine M. Newnam et al 2014^(17)^A three group prospective randomized experimental design was conducted to identify differences in frequency and severity of nasal injuries when comparing various interfaces used during continuous positive airway pressure (CPAP) and identified risk factors associated with injury. Seventy-eight neonates <1500 gm were randomized into three groups: continuous nasal prongs; continuous nasal mask; or alternating mask/ prongs. Participants were block stratified according to BW into four categories: <750 g; 750–1000 g; 1001–1250 g; and 1251–1500 g. Known differences in skin integrity have been demonstrated with the lowest BW infants considered the most vulnerable; thus, stratification was used to keep the groups more homogeneous since it was expected that the <750 g group would contain the fewest patients. All infants were managed with the same type of nasal CPAP delivery system, the Cardinal™ variable flow driver with Air Life™ prongs/mask. Infants transported from the delivery room or outlying hospitals initially treated with nasal CPAP were also eligible for enrolment. Infants that were extubated to other respiratory support devices (high flow nasal cannula, vapor-therm or nasal cannula) based on clinical decision were excluded from enrolment unless nasal CPAP was indicated at a later time. Randomization was conducted by the respiratory therapist at the time of extubation and was accomplished using serially numbered opaque sealed envelopes which were colour coded according to predetermined BW categories (<750 g; 750–1000 g; 1001–1250 g; and 1251–1500 g) supporting block stratification. To determine nasal interface group assignment, the next sequentially numbered envelop was drawn according to the participant's BW and the appropriate nasal CPAP interface was placed on the infant to provide therapy. Repeated measures ANOVA with Bonferroni correction demonstrated that significantly less skin injury was detected in the rotation interface group when compared to both mask and prong groups. In the final stepwise regression model (F = 11.51; R^2^= 0.221; p = 0.006) significant predictors of skin injury included number of days on nasal CPAP (p < 0.001) and current mean post menstrual age (p = 0. 006). Reduced nasal injury was demonstrated using rotating mask/prong nasal interfaces.

Sorabh Goel, Jayashree Mondkar et al 2015 ^(18)^ compared the effectiveness of nasal continuous positive airway pressure delivered by Nasal mask vs Nasal prongs with nasal trauma as secondary outcome. They conducted a randomized controlled, open label, trial at tertiary care level III neonatal unit.118 preterm infants-gestational age (27-34 weeks) requiring nasal continuous positive airway pressure as a primary mode for respiratory distress were included . 61 received nCPAP with nasal Mask as interface and 57 received nCPAP with nasal Prong as interface. Nasal continuous positive airway pressure failure occurred in 8 (13%) of Mask group and 14 (25%) of Prongs group but was statistically not significant (RR 0.53, 95% CI 0.24-1.17) (P = 0.15). The rate of pulmonary interstitial emphysema was significantly less in the Mask group (4.9% vs. 17.5%; RR 0.28, 95% CI 0.08-0.96; P = 0.03). Incidence of moderate nasal trauma (6.5% vs 21%) (P=0.03) and overall nasal trauma (36% vs 58%) (P=0.02) were significantly lower in mask group than in the prongs group.

Aparna Chandrasekaran et al ^(19)^ compared nasal mask vs nasal prong as an interface to deliver nCPAP with FiO2 requirement at 6, 12 and 24 h of CPAP initiation as primary outcome and nasal injury as secondary outcome. they conducted a randomized controlled trial at teaching hospital in new delhi from April 2012 to June 2013. 72 neonates were enrolled in the study —37 were assigned to the nasal mask group and 35 to the nasal prongs group. They found that FiO2 requirement comparable between two groups. The incidence of any grade of nasal trauma during the first 72 h was comparable between the groups (RR 1.07, 95% CI 0.84–1.35, p = .59). The incidence of severe—grade II/III— nasal trauma was, however, significantly lower in the mask group (0 vs. 31%; p < .001). authors concluded that Nasal masks appear to be as efficacious as binasal prongs in providing CPAP with Masks being associated with lower risk of severe nasal trauma.

From The above review of literature it seems both short binasal prongs and nasal mask are equally effective in delivering nCPAP but the measure concern is nasal injury that varies from mild to severe enough requiring corrective surgery, so we are planning to compare whether rotation of nasal interfaces will decrease the incidence of nasal injury as compared to nasal mask or nasal prong alone in neonates on nasal CPAP.

**AIMS & OBJECTIVES**

AIM

To know whether rotation of nasal interfaces will decrease the incidence of nasal injury as compared to nasal mask or nasal prong alone in neonates on nasal CPAP.

OBJECTIVES

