**Primary objective**

1. To identify the incidence and severity of nasal injury at removal of CPAP in all the three groups (i.e. rotation group, mask continue group, prong continue group) based on the objective scoring and a subjective assessment.

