**MATERIAL & METHODS**

Study site:

NICU, Fernandez Hospital, Hyderabad.

Study design:

A Prospective, Randomized, Comparative study.

Sample size with justification:

Assuming an incidence of nasal injury of 50% among the control group at the removal of CPAP from literature review and previous study from our center^(2-6)^. Assuming three group comparisons with an effect size of 30% with 80% power, alpha error of 5% the sample size calculated is 48 in each group and assuming an attrition rate of 10% we need 55 neonates in each group. Sample size was estimated by using Compare k Proportions: 1- way ANOVA Pairwise test ([www.powerandsamplesize.com](http://www.powerandsamplesize.com)). We will enroll patients till a minimum of 55 infants are enrolled in each group.

Time frame:

From september 2016 to march 2018.

Study population

Neonates admitted in NICU for respiratory distress

Inclusion criteria

- All inborn neonates <=30 weeks of gestation and
- Developed respiratory distress (presence of at least two out of three signs: tachypnea > 60/min, intercostal retractions, and expiratory grunt) within 6 hours of life.

Exclusion criteria

- Patients who have Perinatal depression (5 minute Apgar score of ≤3),
- Patients with Life threatening congenital malformations such as congenital diaphragmatic hernia, and trachea-esophageal fistula, other malformations that would prevent from establishing CPAP due to the anatomical defect such as Pierre-Robinson syndrome and choanal atresia
- Conditions where CPAP would be contraindicated such as neonates with poor spontaneous respiratory efforts or apnea, worsening shock, suspected or proven persistent pulmonary hypertension of newborn, severe metabolic acidosis (pH<7.2 with base deficit > -10), severe respiratory acidosis (pH<7.2 with PaCO2>55mmHg) and massive pulmonary hemorrhage

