**Methodology**

Enrolment and randomization process:

Eligible pregnant mothers at a gestational period of <=30weeks will be approached for an informed, written consent for participation in the study. Eligible infants will be stratified as per gestational age, viz. <28 weeks and 28^0/7^-30^6/7^weeks. Those who satisfied the inclusion and exclusion criteria after admission to the neonatal unit will be enrolled in the trial and will be randomly allocated to either mask or prong group.

A second randomization would be done to continue same interface or allocate to rotating group if the infant continues to be on the nasal CPAP after 8 hours of starting CPAP. Those randomized to rotating group will be subjected to mask interface if on prongs and those on prongs will be subjected to mask and the other group would continue with the same interface as before (Figure). Allocation will be done by a web based random number sequence generator ([www.randomization.com](http://www.randomization.com)). Separate person who is not involved in the study will generate the random sequence. Randomization will be stratified for gestation <28 weeks and 28 to 30 weeks. Allocations will be concealed by placing the allocation sequence in opaque, tamper proof, sealed, serially numbered envelopes. The nature of the intervention will prevent us from blinding of the intervention from the investigators as well as the treating team. However, the statistician and the neonatologist reviewing nasal injury images will be blinded from the study allocation details. Further attempts will be made to minimize the bias by maintaining a strict study protocol.

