Gestational age will be calculated primarily based on mothers last menstrual period (LMP). In cases where LMP is unreliable, either an early dating scan or clinical postnatal assessment by new ballard score will be used to calculate the gestational age. Baseline demographic and clinical details such as antenatal steroids, evidence of chorioamnionitis, age at first surfactant, and clinical or echocardiographic evidence of patent ductus arteriosus, severity of illness and severity of respiratory distress [Silverman-Anderson score ^(20)^] will be recorded in a structured case record form. Neonates with onset of respiratory distress in the delivery room will be transferred to the NICU on a T piece device (Neopuff). The duration from birth to onset of intervention and duration of use of T piece will be recorded. The study intervention will start once the study subject is admitted to the NICU.
Interventions**:**

- **CPAP Nasal Mask Group**: The neonate will be given CPAP support by using appropriate sized Drager mask till CPAP is weaned off. The size of the mask chosen will be as per the manufacturer’s instructions.
- **CPAP Nasal Prongs Group**: The appropriate sized Hudson prongs as per the manufacturer’s instructions will be used for providing CPAP. The prongs will be continued.
- **Rotating group (Mask with Prongs and vice versa)**: The appropriate sized Drager mask and Hudson prongs will be rotated every 8 hourly (each nursing shift) for delivering CPAP. Care will be taken during these changes to minimize the duration of off-CPAP period.

Heating and humidification of gases: The gas delivered in both the devices was heated and humidified to attain a gas temperature of 37 degree C at the level of the nostrils. The humidifier used in both the groups had a flow-based servo-humidification control mechanism to ensure appropriate humidification. Protocol for titration, weaning and removal of CPAP is given in figure 1.

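### Infants are re-randomised to continue or rotate within a starting interface, but the plan compares three groups, so a mask–prong difference can be mistaken for a benefit of rotation

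*Protocol*

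**What the plan says.** The aim under AIMS & OBJECTIVES is "To know whether rotation of nasal interfaces will decrease the incidence of nasal injury as compared to nasal mask or nasal prong alone". The Introduction uses the same 'or': "in comparison to use of a single interface (prong or mask").

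The Methodology randomises twice. Infants first go to mask or prong. Then, for those still on CPAP after 8 hours, "A second randomization would be done to continue same interface or allocate to rotating group". The flow chart shows the result: a rotation group under the initial mask group and another under the initial prong group, each beside its own continuing group. For the rotating infants, "The appropriate sized Drager mask and Hudson prongs will be rotated every 8 hourly (each nursing shift) for delivering CPAP".

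The primary objective treats these as three groups: injury is to be identified "in all the three groups (i.e. rotation group, mask continue group, prong continue group"). The sample size rests on a single control rate: "Assuming an incidence of nasal injury of 50% among the control group at the removal of CPAP". The Statistical analysis section names chi-square with continuity correction or Fisher's exact test at P<0.05. It does not say which groups are contrasted, and the starting interface plays no part in it.

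**The concern.** A rotating infant spends roughly half of the CPAP time on each interface. If alternating has no effect of its own and risk simply averages, the rotation group falls midway between the two continuous groups: better than the worse interface and no better than the other. A three-group test can then be significant purely because mask and prong differ. A rotation-versus-prong test can be significant because rotating infants spent less time on prongs. Neither result shows that alternation protects.

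The Protocol's own literature makes this possible. One cited trial reports "overall nasal trauma (36% vs 58%) (P=0.02) were significantly lower in mask group than in the prongs group". The randomisation was built to answer a cleaner question, rotate or continue from the same starting interface, and the stated analysis does not use it. At stake is whether a positive result can be attributed to rotation.

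**Working it through.** **The plan's own figure.** Inputs from the sample-size paragraph: control 50%, effect 30% (read as absolute, so rotation 20%), power 80%, alpha 5%, pairwise method for k proportions. With three pairwise comparisons:

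n = [pA(1−pA) + pB(1−pB)] × [(z(1−0.05/6) + z(0.80)) / (pA−pB)]²
= (0.25 + 0.16) × [(2.394 + 0.842)/0.30]² = 47.7, so 48.

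This matches the stated 48. Attrition: 48/0.90 = 53.3, so 54 against the stated 55. The number is right for its inputs. Those inputs set both controls at 50%.

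**Scenario with no effect of alternation.** Mask 36% and prong 58% come from the cited trial. Rotation = (36 + 58)/2 = 47% is an assumption (linear averaging, half the time on each interface). n = 55 per arm.

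*Three-group test.* The noncentrality is n × Σ(p−p̄)² / [p̄(1−p̄)] = 55 × (0.11² + 0.11² + 0) / (0.47 × 0.53) = 5.34. The rotation arm contributes zero; all of it comes from mask versus prong.

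*Rotation versus prong, uncorrected.* Pooled rate 0.525.
- SE under equality = √(0.525 × 0.475 × 2/55) = 0.0952
- SE under the alternative = √[(0.58 × 0.42 + 0.47 × 0.53)/55] = 0.0946
- Power = Φ[(0.11 − 1.96 × 0.0952)/0.0946] = Φ(−0.81) ≈ 21%

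Simulation, two-sided 0.05, counting only results in rotation's favour (the three-group test has no direction; the continuity correction applies only to two-by-two tables):

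| Mask / prong / rotation, n per arm | Three-group test | Rotation beats prong, uncorrected | Corrected | Rotation beats mask |
|---|---|---|---|---|
| 36 / 58 / 47%, 48 | 48–49% | 19% | 14% | about 0.1% |
| 36 / 58 / 47%, 55 | 54–55% | 20% | 15% | under 0.1% |
| 50 / 50 / 50%, 55 | 5% | 2% | 1.5% | 2% |

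If the pairwise level were 0.05/3, as the sample-size method implies but the Statistical analysis section does not state, the 15–20% at 55 per arm would fall to about 8–11%.

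A second cited trial gives 0% versus 31% for grade II/III trauma. Averaging gives 15.5%, and rotation then beats prong in about 40% (corrected) to 49% of trials at 55 per arm. That grading covers the first 72 hours and is not this trial's score six hours after CPAP removal, so it only indicates the range.

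**Stratified rotate-versus-continue test.** Mantel-Haenszel with two strata by starting interface, the rotation group split evenly by start (an assumption; no allocation ratio is given for the second randomisation). With no alternation effect, in both unequal scenarios above, it favours rotation in about 2.4–2.8% of trials, close to the nominal one-sided 2.5%: the apparent gain among prong starters cancels the apparent loss among mask starters. Under the plan's own 50% versus 20%, with 48 per arm (24 rotating and 48 continuing in each stratum), its power is about 95%, against 88% for one uncorrected pairwise test at 0.05.

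**The case against.** Five points on the other side deserve weight.

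1. A reader might infer that the Protocol declares success if rotation beats either comparator. It does not. The aim names comparators and sets no success rule, and 'or' can fairly mean each of them. What stands is that the text leaves this open.
2. A reader might infer that the trial would go on to recommend a worse practice. There is a separate continuous-mask group, and the primary objective covers all three groups, so the pattern would be visible to anyone who looked. The sample-size method is pairwise and so includes rotation versus mask.
3. A reader might take it as established that masks are gentler. The cited evidence is mixed. One trial found no difference in trauma (p = 0.5), another had two injuries in each group, and the trial with 0 versus 31% for grade II/III found any-grade injury comparable (RR 1.07, p = .59).
4. In the 36/58/47% scenario rotation really does carry less risk than prong, and mask really differs from prong. The tests are not wrong about those contrasts. The error would lie in crediting alternation. Linear averaging is itself an assumption, and one cited trial reports different injury sites for the two interfaces.
5. Contrasts are often left to a statistical analysis plan, which is not shown. That excuses a missing list of contrasts. It does not remove the mismatch inside the Protocol between a continue-or-rotate randomisation and a three-group comparison with one control rate.

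**Conclusion.** The point holds as a mismatch between randomisation and analysis. With unequal controls (36% and 58%), no alternation effect and 55 per arm, the three-group test is significant in about 55% of trials, and rotation appears better than prong in 15–20%. This rests on risk averaging linearly over roughly equal time on each interface, which is only approximate because the first 8 hours are all on the starting interface. It also rests on a real mask–prong difference. If the two are equal, the three-group test returns to about 5% and a chance win over either control to about 3–5%. The documents do not support saying that the plan accepts a win over either arm, or that it will lead to an inferior recommendation. They do support analysing by the randomisation actually performed, which removes the ambiguity and, under the plan's own assumptions, gains power.

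**What to change.** - Make the primary comparison rotate versus continue, stratified by starting interface: mask-start rotation against continuous mask, prong-start rotation against continuous prong, then combined, for example by Mantel-Haenszel.
- Report rotation versus mask and rotation versus prong separately, and describe a difference from prong alone as a finding versus prongs only. The single strata are small (about 27 against 55), so they support the combined result and do not replace it.
- State in the aim that rotation is compared with each of the two single interfaces, and give mask and prong their own assumed rates in the sample-size paragraph.
- A formal rule that rotation must beat both arms is optional. It reduces the chance of wrong credit to about 0.1% or less in the unequal scenarios. If the mask rate is 36% and rotation 20%, however, power against mask is only about 41% (48 per arm) to 46% (55 per arm), and 80% would need about 123 per arm.

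The cost is wording and a named primary comparison. The study form already records the initial choice of interface. The one loss is that a win over prongs alone no longer supports a general claim for rotation.
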